## Abstract

**Background:**

Metacognitive dysfunction has been widely recognized as a feature of schizophrenia. As it is linked with deficits in several aspects of daily life functioning, improvement of metacognition may lead to improvement in functioning. Individual psychotherapy might be a useful form of treatment to improve metacognition in patients with schizophrenia; multiple case reports and a pilot study show promising results. The present study aims to measure the effectiveness of an individual, manual-based therapy (Metacognitive Reflection and Insight Therapy, MERIT) in improving metacognition in patients with schizophrenia. We also want to examine if improvement in metacognitive abilities is correlated with improvements in aspects of daily life functioning namely social functioning, experience of symptoms, quality of life, depression, work readiness, insight and experience of stigma.

**Methods/Design:**

MERIT is currently evaluated in a multicenter randomized controlled trial. Thirteen therapists in six mental health institutions in the Netherlands participate in this study. Patients are randomly assigned to either MERIT or the control condition: treatment as usual (TAU).

**Discussion:**

If proven effective, MERIT can be a useful addition to the care for schizophrenia patients. The design brings along some methodological difficulties, these issues are addressed in the discussion of this paper.

**Trial registration:**

Current Controlled Trials: ISRCTN16659871.

## Background

Metacognitive dysfunction has been widely recognized as a feature of schizophrenia
[1,2] and is linked with deficits in daily life functioning
[3-5]. Over the years, the construct of metacognition has been defined in different ways. All definitions describe a general capacity to think about thinking
[6]. Flavell
[7] was one of the first to use the term. In his view metacognition is closely related to ‘cognitive monitoring’: the ability to observe one’s own cognitive processes and to detect errors in these processes. Moritz & Woodward
[8] provide a more specific definition that targets dysfunctional thought processes in particular, defining metacognition as ‘being aware of cognitive distortions’. Wells
[9] includes thinking about feelings. He also describes the important role of metacognition in eliciting reactions triggered by these thoughts and feelings. Based on the work of Semerari et al. on metacognition
[10], Lysaker et al.
[11] propose to integrate different definitions and propose a definition that involves four fundamental aspects:

– Self-reflectivity: the ability to think about one’s own thoughts and emotions;

– Understanding the other’s mind: the ability to think about the thoughts and emotions of others;

– Decentration: the ability to understand that you are not the center of the world and people’s lives continue when you are not around;

– Mastery: One’s ability to use the three aspects above to define psychological problems and adequately deal with them.

In this definition, metacognition refers to a spectrum of activities, which involves thinking about thinking and stretches from consideration of discrete psychological phenomena (for example: recognizing an isolated thought) to the synthesis of discrete perceptions into an integrated representation of self and others
[12]. Metacognitive capacities “allow persons to form a detailed picture of their own mental states, of the wishes and intentions of the others, and of the inner and social cues that trigger psychological pain, and thereby to cope with challenges and solve complex social problems […]. In the larger frame they make it possible for persons to make sense of their dilemmas, to find meaning in life, and to ultimately adapt to a changing environment”
[2]. In this way metacognitive dysfunction is more than just a missing skill. It is the inability to make complex sense of experience and integrate interpersonal information into a larger whole
[12].

Several instruments have been developed to assess elements of metacognition. Most of these instruments capture more discrete aspects of the concept as it is defined above, for example the Meta-Cognitions Questionnaire (MCQ)
[13] which measures beliefs about worries and intrusive thoughts and the Davos Assessment of Cognitive Biases Scale (DACOBS)
[14], measuring cognitive biases. Semerari et al.
[10] developed the Metacognition Assessment Scale (MAS) based on the four elements of metacognition. This instrument was originally designed to measure metacognition in people with personality disorders. Lysaker et al.
[11] have shortened this instrument and adapted it for use with people with psychotic disorders (MAS-A).

Metacognition is linked to aspects of daily life function of patients with schizophrenia in several ways. Better metacognitive mastery is linked to better social cognition and more insight
[2,15] and metacognition has been found to mediate the impact of neurocognitive deficits on social function, after controlling for symptoms
[16]. Lower levels of metacognition correlate with less favorable reports of the subjective experience of recovery
[17] and lower levels of functional competence
[18]. In addition to these daily life aspects, impaired metacognition has also been associated with low quality of therapeutic alliance
[19] and more severe negative symptoms
[11,20,21]. Moreover, lower levels of metacognition predict future severity of negative symptoms, even after controlling for concurrent levels of negative symptoms
[22].

Based on the above, it is hypothesized that improved metacognition will result in improved daily life functioning. Metacognition might be a feasible target for treatment of people with psychotic disorders. If an intervention would be capable of improving metacognitive capacity, it would enable persons with schizophrenia to achieve more complex understanding of themselves and others and thus find ways to actively direct their recovery process. Individual psychotherapy might be a useful form of treatment to improve metacognition. Several forms of psychotherapy have successfully promoted metacognitive capacity in persons with various mental disorders other than psychosis
[23], including work from a psychoanalytic
[24] and a cognitive frame of reference
[25]. It has also been suggested that some of these therapeutic procedures could be modified for treatment of people with schizophrenia
[26]. If metacognition is conceptualized as a trait-like capability that varies along a continuum from good to impoverished, psychotherapy might provide a place to practice such capacities in increasing degrees of complexity, leading to enhancement of metacognitive capacity. Manualized procedures for a metacognitive psychotherapy for schizophrenia have been proposed
[26] and multiple detailed case reports and a pilot study have documented the acceptability of the treatment and positive outcomes
[27-33]. The present paper presents the design of a randomized controlled multicenter trial that aims to measure the effectiveness of the Metacognitive Reflection and Insight Therapy (MERIT) in improving metacognition.

### Research aims

Primary objective of this study is to investigate whether Metacognitive Reflection and Insight Therapy improves metacognitive abilities in people with schizophrenia. Secondary objective is to examine whether improvements in metacognitive capacity lead to improvements in quality of life, social functioning, depression, symptoms, stigma sensitivity and work readiness. Neurocognition is adopted in the assessment as well, as it may function as a mediator between metacognition and functioning. A cost-effectiveness analysis will be performed at the end of the study.

## Methods/Design

The study is funded by Fonds NutsOhra, GGZ Drenthe, GGZ Friesland and the Institute for Post master Psychology in the Northern Netherlands (PPO). The study has been approved by the medical ethical board of University Medical Center Groningen, Groningen (number: METc2013.124, date: november 2013), and is conducted in accordance with the principles of the Declaration of Helsinki. Trial number: ISRCTN16659871 (Current Controlled Trials).

### Design

The study is designed as a multicenter randomized controlled trial including an intervention group receiving Metacognitive Reflection and Insight Therapy (MERIT) and a control group receiving treatment as usual (TAU).

### Participants/setting

Participants in the study are people with schizophrenia or schizoaffective disorder and impaired metacognitive abilities. A total of 120 participants will be included from six mental health care institutions in the Netherlands. Thirteen therapists who work in these facilities will be trained to give the therapy.

Inclusion criteria are:

Impaired metacognitive skills, as measured by the Metacognition Assessment Scale (MAS-A);

Diagnosis of schizophrenia or schizoaffective disorder, according to DSM-IV-TR criteria;

Being able to give informed consent;

18 years or older;

No change in medication in the past thirty days.

Exclusion criteria are:

Acute psychosis (mean score of PANSS positive symptoms >4);

Co-morbid neurological disorder;

Substance dependence (not substance abuse as measured with the MINI Plus);

Impaired intellectual functioning (IQ <70)

### Sample size calculation

Sample size was computed with a two-sided test using the IBM SPSS Sample Power program (Biostat, M. Borenstein), http://www.power-analysis.com/about_biostat.htm. The effect size of MERIT is not known. We chose to adopt the common convention in such instances, and set our effect size at 0.5
[34]. This is based on the consideration that should the effect size be lower, results would probably not be clinically relevant
[35,36]. In order to show medium effect sizes (0.5) with an alpha of 0.05 and a power of 0.80, a minimum of 48 subjects in both groups is required. This means that there is an 80% likelihood that the study will detect a statistically significant effect if such exists, and allows us to conclude that the mean metacognition score differs for MERIT versus TAU. Because this is a time consuming trial with people with a severe mental illness, we assume that the percentage of dropouts will be 20%. This means that for every 120 subjects enrolled in the study, 24 will be lost to follow-up or withdraw informed consent and will be excluded from the analysis. Therefore we will select 60 patients in the intervention group and 60 patients in the control group including 12 extra participants in each group to compensate for the anticipated missing data.

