## Discussion

With this multicenter randomized controlled trial, we intend to investigate the effectiveness of a manual-based psychotherapy aimed at improving metacognition and daily life functioning of patients with schizophrenia. Metacognition is a complex, multi-dimensional concept, involving four main aspects: self reflection, understanding the mind of the other, decentration and mastery. It not only refers to the ability to detect and consider discrete psychological phenomena (for example: recognizing a thought), but also to the ability to integrate these phenomena into an integrated, complex representation of self and others
[12]. MERIT tries to enhance these synthetic metacognitive processes through constant reflection in the interpersonal relationship. In this way, the patient learns to reflect on him/herself in ever more complex ways. We hope this will result in structural changes in metacognitive processes in patients with schizophrenia, and hope this in turn will lead to structural, lasting improvements of daily life functioning of the patient. This design brings along some methodological difficulties, especially the risk of drop-out over time. We hope to account for this by including 20% extra patients in the trial to ensure statistical power will be maintained despite patient attrition.

Most interventions for people with schizophrenia in the Netherlands target first-episode patients within five years after the first psychotic episode. Care for chronic patients usually focuses on support and structure instead of recovery. MERIT can be used with patients who are chronically mentally ill, and case studies show promising results. If proven effective, this therapy might be a useful addition to the care for chronic schizophrenia patients.

Furthermore, some patients benefit less from usual interventions such as psycho-education and cognitive behavioral therapy. It could be hypothesized that these patients are not able to form complex representations of self and others, which makes it difficult to engage in therapy. Improving metacognition might prove a necessary step for these patients to benefit from other interventions and enhance daily functioning.

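### On the stated inputs (two-sided 5% test, effect size 0.5), 48 analysed patients per group gives about 68% power, not 80%; 80% needs 64 per group

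*Protocol article*

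**What the plan says.** The section Sample size calculation states that "Sample size was computed with a two-sided test", sets the effect size at 0.5 by convention, and concludes that "with an alpha of 0.05 and a power of 0.80, a minimum of 48 subjects in both groups is required". It interprets this for the reader: "This means that there is an 80% likelihood that the study will detect a statistically significant effect if such exists". The target is a difference in mean metacognition score between MERIT and TAU. The section treats a smaller effect as probably not clinically relevant.

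It then assumes 20% dropout, with dropouts left out of the analysis, and adds 12 patients per group. This gives 60 per group and 120 in total, and it confirms that 48 is a per-group figure (60 − 12 = 48; 96 analysed overall). The Discussion returns to the extra patients, whose purpose is "to ensure statistical power will be maintained despite patient attrition".

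The sample size section names no baseline-outcome correlation, covariate or repeated-measures gain. The section Analysis describes a multilevel model over the assessment times, with dummy variables and their interactions as fixed effects. It does not write the model out or name the contrast that decides the trial.

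**The concern.** Every input needed to check the figure of 48 is printed in one paragraph, and the result is a quarter below what those inputs require. The protocol regards 0.5 as roughly the smallest effect worth finding, so power at exactly that value is what the trial was sized for. If the stated 80% is really about 68%, the risk of missing that effect under the calculation described is about 32% rather than 20%. The assurance in the Discussion would also fail, because the power falls short even before any patient is lost.

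**Working it through.** **Inputs, all from Sample size calculation:** two-sided test; alpha 0.05; power 0.80; standardised difference d = 0.5; two independent groups, 1:1; 48 analysed per group; 20% dropout.

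**1. Attempt to reproduce 48.** Normal approximation for two means:

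n per group = 2 × (1.960 + 0.842)² / d² = 2 × 7.85 / 0.25 = 62.8, so 63.

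The noncentral t distribution gives 63.8, so **64 per group**. Neither is near 48.

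**2. Power at 48 per group.** Noncentrality = d × √(n/2) = 0.5 × √24 = 2.449.
- Normal approximation: Φ(2.449 − 1.960) = Φ(0.490) = 68.8%.
- Noncentral t, 94 degrees of freedom: **67.9%**.
- Effect detectable with 80% power at 48 per group: d = 0.578.

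**3. Power with no dropout.** At 60 per group, noncentral t gives 77.5%.

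**4. Dropout step.** 48 / 0.8 = 60, so the inflation is done correctly and the error lies in the 48. From the right starting point, 64 / 0.8 = 80 per group, or 160 enrolled, against 120.

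**5. Where 48 could have come from.**

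| Calculation | n per group | Power at 48 | Fit with the text |
|---|---|---|---|
| Two-sided 0.05 | 64 | 67.9% | As stated |
| One-sided 0.05 | 51 (50.2 rounded up) | 78.4% | Contradicts the stated two-sided test |
| Baseline-adjusted, r = 0.5, two-sided 0.05 | 64 × (1 − 0.25) = 48 | 79.9% | No correlation is stated |

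**6. How far the analysis model could change the picture.** Take 48 per group, an effect of 0.5 and equal variances at each visit. The value of r is an assumption, because the document gives none. The effective effect size is 0.5 divided by the square root of the variance factor.

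| Contrast | Variance factor | r = 0.3 | r = 0.5 | r = 0.6 |
|---|---|---|---|---|
| Outcome adjusted for baseline | 1 − r² | 72% | 80% | 86% |
| Change to one visit, baseline free | 2(1 − r) | 54% | 68% | 77% |
| Mean of post-treatment and follow-up minus free baseline | 1.5(1 − r) | 66% | 80% | 88% |

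The third row assumes the same effect at both visits and one common correlation between all visits. The factor is (1 + r)/2 + 1 − 2r = 1.5(1 − r).

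**The case against.** The best defence is that the trial will not be analysed by an unadjusted comparison at one visit. The primary measure is taken at intake, post-treatment and follow-up (Table 1), and the Analysis section plans a repeated-measures model. A full protocol behind this condensed article might hold a correlation of 0.5, which reproduces 48 exactly. This stands in part: the text cannot show which step produced 48, and true power could exceed 68%. It does not rescue the statement as printed, which derives 80% from listed inputs that do not give it.

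A reader might infer four stronger things, none of which the document supports.
- **That the trial's actual chance of missing d = 0.5 is one in three.** This holds only for the unadjusted single-visit comparison. Under the contrasts in step 6, power runs from 54% to 88%, depending on r and on the contrast.
- **That the planned model cannot deliver the gain from baseline.** A free baseline is the natural reading of interactions fitted as fixed effects, but the model is not written out. Pooling both later visits against a free baseline also reaches 80% at r = 0.5.
- **That a one-sided test was used.** The one-sided answer of 51 is close to 48, but so is the baseline-adjusted one. The origin is conjecture.
- **That a null result will be misread as evidence against MERIT.** Nothing in the document addresses how a null result would be interpreted.

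**Conclusion.** The sample size statement is wrong as written. For a two-sided 5% comparison of two group means at d = 0.5, 80% power requires 64 analysed patients per group, and 48 gives about 68% (67.9% by noncentral t, 68.8% by normal approximation). The shortfall is 12 points of power, or 16 analysed patients per group, too large to be rounding or a software difference. It persists with complete follow-up (77.5% at 60 per group). The arithmetic needs no assumption beyond the printed inputs and an ordinary two-sample comparison.

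Power under the multilevel model remains undetermined, because it turns on an unstated correlation and an unnamed primary contrast.

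**What to change.** 1. **Correct the statement.** Say that 48 analysed per group gives about 68% power for d = 0.5, and 80% power for d of about 0.58, with a two-sided 5% test. Amend the 80% claim in Sample size calculation and the claim in the Discussion that power is maintained. If 48 did rest on a baseline correlation, state that correlation and its basis instead. This costs only wording, and a less favourable stated power if no correlation can be supported.

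2. **Recover power without more patients, as far as possible.** Make the primary analysis adjust for the intake MAS-A score, either as a covariate or by constraining the two arms to equal baseline means, and state the assumed correlation. Table 1 places this score before randomisation, so no new data are needed. Power at 48 per group is then about 72%, 80% or 86% at r = 0.3, 0.5 or 0.6. This should not be presented as a certain repair: 80% is reached only if r is about 0.5 or more. Entry requires scores below cut-off on at least three of the four MAS-A scales, and selecting on the baseline in this way may lower r. The cost is one stated assumption and a small change to the model description.

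3. **If the 80% claim is to stand on the inputs as printed,** the consequence is 80 per group, or 160 enrolled at 20% dropout: 40 more than planned.

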### Procedure

Thirteen therapists in six Dutch mental health care institutions will select all patients in their caseload that meet the inclusion criteria. They will answer four screening questions concerning these patients’ metacognitive abilities on a 10 point scale (see Section Screening for the screening questions). The therapists approach the patients that score below the cut-off of the screening and ask them if they are interested in participation. The names of the interested patients will be coded by the therapist. Out of these coded names a random selection will be chosen by the researchers to prevent selection bias. The selected coded names will be transferred back to the therapists, who will then provide the contact information of these patients to the researcher and will inform the patients that an assessor will approach them. The assessor will call the patient and answer any questions the patient may have about the study. Every participant has a two-week period to consider participation. If the patient is still willing to participate after this period, an assessor will make an appointment for an intake to confirm that the patient fulfills all of the study’s inclusion criteria. The intake will take approximately 1,5 hours. Patients that are included in the study will be randomly allocated to the treatment condition (MERIT) or treatment as usual (TAU). The randomization is conducted separately for each center and procedures will start directly after the first participants are included. Randomization will be done by a party independent from the trial research team. Results of the randomization process will be passed on to the onsite therapists. Block randomization will be used to ensure that the number of patients will be balanced over condition. Assessors will be blind to the subject’s condition. Rater blinding will be verified after the assessment. For therapists, it is of course not possible to be blind for condition. After assignment to intervention or control condition, the assessor plans a second appointment with the patient for baseline assessment. A research assistant, blind to treatment or control condition, who is not involved in the patient's treatment, will carry out this assessment. This assessment will take approximately 1.5 hours. Thereafter, the individual treatment will start. Onsite clinical psychologists that have partaken in the three-day MERIT training will provide the intervention. Participants in the control condition will receive treatment as usual (TAU). After forty sessions of treatment or forty weeks in the control condition, the assessment will be repeated (post-treatment). Follow-up assessment will take place six months after completion of the intervention.

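### Excluding patients lost to follow-up or withdrawing consent makes the comparison one of assessment completers; over-enrolment restores numbers but not the randomised comparison

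*Protocol article*

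**What the plan says.** The Sample size calculation section sets a minimum of 48 analysable patients per group, assumes 20% drop-out and enrols 60 per group. It then gives a rule for the patients lost: "24 will be lost to follow-up or withdraw informed consent and will be excluded from the analysis". The 12 additional patients per group are described as compensation for the missing data.

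The Discussion names drop-out over time as the main methodological difficulty and gives the same answer: "We hope to account for this by including 20% extra patients in the trial". The stated purpose is to maintain power.

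Three other places bear on the point:

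- The Analysis section plans a multilevel model with subject and assessment time as levels. It mentions no exclusion.
- Table 1 places the MAS at intake, before randomisation, and again at post-treatment and follow-up.
- The Procedure section times the second assessment differently in the two arms: "After forty sessions of treatment or forty weeks in the control condition, the assessment will be repeated". Follow-up comes six months after the intervention ends.

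**The concern.** Over-enrolment deals with one consequence of drop-out, which is fewer patients and less precision. It does not deal with the other, which is that those who remain may no longer be comparable between arms. Loss to follow-up and consent withdrawal happen after randomisation. If the reasons for them differ between arms and are related to outcome, the remaining patients are not a fair sample of each arm as randomised.

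That is plausible here. MERIT asks for forty individual sessions of 45 minutes, control patients continue usual care, and the therapists know the allocation. At stake is the main MERIT-TAU comparison, with a fifth of the randomised patients expected to be left out of it.

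The exclusion also goes further than the planned model requires. A multilevel model can use incomplete series. Read literally, the rule would discard a patient who has post-treatment data but is lost before the six-month assessment, although that patient has an outcome at the end of treatment.

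**Working it through.** **1. The plan's drop-out arithmetic.** Inputs from the Sample size calculation section: 48 analysable per group, 20% loss, 60 per group enrolled.

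- Enrolment: 48 / (1 - 0.20) = 60 per group, 120 in total.
- Expected loss: 0.20 x 120 = 24, or 12 per group. Analysed: 120 - 24 = 96, or 48 per group.

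This step reproduces. The base figure of 48 does not: effect size 0.5, two-sided alpha 0.05 and power 0.80 need 64 per group by t-test, and 48 per group gives power 0.68. That is a separate matter. The present point does not depend on it.

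**2. What exclusion can do to the estimate.** Let p be the share lost in one arm and g the difference, in SD units, between that arm's completers and the mean its lost patients would have had. The arm's full mean is (1 - p) x completer mean + p x lost mean, so

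completer mean - full mean = p x g.

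If loss in the other arm is unrelated to outcome, the between-arm difference shifts by p x g. The value p = 0.20 is the plan's own. The values of g, and the restriction to one arm, are assumptions.

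- g = 0.5: 0.20 x 0.5 = 0.10 SD, which is 0.10 / 0.5 = 20% of the target effect.
- g = 0.75: 0.20 x 0.75 = 0.15 SD, which is 0.15 / 0.5 = 30% of the target effect.
- g = 0: no shift; only precision is lost.

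**3. Effect on the error rate.** With no true effect and n analysed per group, the t statistic has 2n - 2 degrees of freedom and noncentrality shift x sqrt(n/2). At n = 48 there are 94 degrees of freedom, and sqrt(48/2) = sqrt(24) = 4.90.

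| Shift (SD) | Noncentrality | Two-sided rejection rate, nominal 5% |
|---|---|---|
| 0.10 | 0.10 x 4.90 = 0.49 | 7.7% |
| 0.15 | 0.15 x 4.90 = 0.73 | 11.2% |

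**4. Does enrolling more help?** Hold the shift at 0.10 SD and increase the number analysed per group:

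- 48 per group: 7.7%
- 96 per group: 10.6%
- 192 per group: 16.5%

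The bias stays the same while the standard error shrinks, so the false-positive rate rises.

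**5. Would the multilevel model remove this bias?** Largely not in this scenario. A patient lost before post-treatment contributes only the intake MAS score. If the deficit among those lost is unrelated to the intake score, that score carries no information about it. A simulation of the 0.10 SD case (60 per arm, 20% loss, assumed intake-to-post correlation 0.5) gave a bias of about 0.10 SD both among completers and when the intake scores were kept under missing at random. The model helps where observed scores predict loss, and it keeps patients who miss only the last assessment.

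**6. The sections side by side.** The Sample size calculation removes patients with incomplete follow-up. The Analysis section describes a model that can keep them. Table 1 gives every randomised patient an intake MAS score. The exclusion is therefore not needed by the model and sits badly with it. In Procedure, a control patient's post-treatment assessment has a calendar time (forty weeks). A MERIT patient's depends on completing forty sessions, so its timing is unclear for someone who stops earlier.

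**The case against.** The strongest reply is about location. The sentence stands in a sample-size paragraph, where it explains why 48 becomes 60, and the Analysis section states no exclusion. One may fairly read this as an inconsistency between two sections rather than a settled completer analysis. That has weight, but the exclusion is stated outright and the Discussion takes the same view of attrition. An analysis plan that kept all randomised patients would contradict the sentence, so it needs correcting on either reading.

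Three stronger readings are tempting, and the documents do not support them.

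- *Patients who stop therapy early are excluded.* A reader might infer this from the forty-session timing. The rule covers only loss to follow-up and consent withdrawal. Nothing says that a patient who stops sessions is not assessed or not analysed. Only the assessment time is unclear.
- *The bias favours MERIT.* The plan assumes equal loss, 12 per group, and attributes it to the burden of the trial and the severity of illness, which apply to both arms. Control patients also face the repeated assessments. Control patients who deteriorate, or MERIT patients who improve, might be the ones lost, and either would bias against MERIT.
- *The 7.7% and 11.2% measure what the exclusion sentence costs.* They describe outcome-dependent loss in one arm. Deleting the sentence and relying on missing at random would leave most of that bias in place.

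**Conclusion.** The point holds in this form: the article states a rule that removes an expected 24 of 120 randomised patients because of events after randomisation, and its only remedy is a larger sample, which cannot restore the randomised comparison. The rule also conflicts with the article's own multilevel model.

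The direction and size of any bias cannot be derived from the documents. The 0.10 to 0.15 SD shift, with error rates of about 7.7% to 11.2%, is an illustration. It rests on 20% loss, a deficit of 0.5 to 0.75 SD among those lost, selection in one arm only, and 48 analysed per group. If loss is unrelated to outcome, the cost is precision alone.

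**What to change.** - In the Sample size calculation section, replace the exclusion with a statement, consistent with the Analysis section, that all randomised patients are analysed in the arm assigned, using all available assessments in the multilevel model under missing at random. Keep data up to consent withdrawal as the consent allows.
- In Procedure, state that patients who stop sessions early are still invited to the post-treatment and follow-up assessments, and say when these take place.
- Report loss, with reasons, by arm.
- Add one missing-not-at-random sensitivity analysis, for example shifting the unobserved scores of lost patients in one arm and then the other by a stated range. This is needed because the likelihood-based model alone does not correct outcome-dependent loss before post-treatment.
- In the Discussion, limit the claim for over-enrolment to precision.

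The cost is some wording, a little more analysis work, and assessment follow-up of early stoppers within the 120 already planned. The estimate may be smaller than among completers. The assessment invitations should be settled early, because outcomes not collected at the time cannot be recovered.
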